# Clinical trial protocol

## SYNOPSIS

|                       |                                                                                                                                                                                                                                                                                                                                                                                                                                                                                                                                                                                                                                                                                                                                                                                                                                                                                                                                                                                                                                           |
|-----------------------|-------------------------------------------------------------------------------------------------------------------------------------------------------------------------------------------------------------------------------------------------------------------------------------------------------------------------------------------------------------------------------------------------------------------------------------------------------------------------------------------------------------------------------------------------------------------------------------------------------------------------------------------------------------------------------------------------------------------------------------------------------------------------------------------------------------------------------------------------------------------------------------------------------------------------------------------------------------------------------------------------------------------------------------------|

| PRIMARY OBJECTIVE  | Post-exertional malaise (PEM)
symptoms of post-COVID-19 subjects
and age/sex matched controls in
response to 3 different exercise trials.                                                                                                                                                                                                                                                                                                                                                                                           |
| STUDY DESIGN       | Interventional, randomized, single-
center, two-arm crossover study                                                                                                                                                                                                                                                                                                                                                                                                                                                                       |
| STUDY ARMS         | 
1) Post-COVID-19 syndrome patients
 
2) Age- and sex-matched healthy control
subjects
                                                                                                                                                                                                                                                                                                                                                                                                                                        |
| SAMPLE SIZE        | 40 post-COVID-19 syndrome patients
and 40 age- and sex-matched healthy
controls                                                                                                                                                                                                                                                                                                                                                                                                                                                        |
| INCLUSION CRITERIA | 
1. Age range 18–64 years
 
2. None of the patients' complaints have
been present before March 2020
 
3. Verified positive COVID-19 PCR test
(for the post-COVID-19 group only)
 
4. Symptoms have persisted for at least
3 months after COVID-19 infection
 
5. Reported worsening of symptoms after
exertion
 
6. No previous history of cardiovascular
disease
 
7. No history of generalized anxiety
disorder or somatic symptom disorder
 
8. Written informed consent
 |

|                           |                                                                                                                                                                                                                                                                                                                                                                                                                                                                                                   |
|---------------------------|---------------------------------------------------------------------------------------------------------------------------------------------------------------------------------------------------------------------------------------------------------------------------------------------------------------------------------------------------------------------------------------------------------------------------------------------------------------------------------------------------|
| EXCLUSION CRITERIA | 
 
1. Age outside the range of 18–64 years
 
2. Patient's symptoms occurred before March 2020
 
3. No verified positive COVID-19 PCR test
 
4. Symptoms disappeared within 3 months of COVID-19 infection
 
5. Has not reported worsening of symptoms after exertion
 
6. Current or previous cardiovascular disease
 
7. Current or history of generalized anxiety disorder or somatic symptom disorder
 
 |
| SCHEDULE           | 
Recruiting first participant: September 2022
 
Recruiting last participant: July 2023
 
Study planned completion: July 2024
                                                                                                                                                                                                                                                                                                                                                      |

## **BRIEF SUMMARY**

The post-COVID-19 syndrome poses an unprecedented challenge to modern society, affecting millions of people worldwide. Persistent fatigue and exercise intolerance are among the most common complaints of these subjects. The mechanisms of exercise intolerance in post-COVID-19 subjects remain yet unknown, which make the rehabilitation efforts complex and challenging. The overall goals of this project are to: 1) improve physiological understanding of symptoms in this clinical condition, 2) elucidate plausible mechanisms to explain exercise intolerance/symptom exacerbation, and finally 3) provide knowledge that can be directly applied in the clinical setting to improve diagnosis, care, and individualized rehabilitation of subjects with post-COVID-19 syndrome. Post-COVID-19 subjects and age/sex matched healthy controls will undertake a comprehensive set of physiological and functional assessments, followed by 3 experimental visits (in a randomized order), where acute exercise responses will be assessed in either continuous moderate intensity aerobic exercise, high intensity interval exercise, or strength training. The same set of physiological assessments will also be performed after 1 year in both post-COVID-19 subjects and healthy-matched controls to better understand the time course of the syndrome.

## **ADMINISTRATIVE INFORMATION**

### **1. TITLE**

**EX**ercise Into**LE**rance in post-COVID-19 patients (EXILE) - a randomized clinical trial

### **2. TRIAL REGISTRATION**

This study is registered in [ClinicalTrials.gov](https://clinicaltrials.gov/ct2/show/study/NCT05445830) NCT05445830 (2023-07-02).

### **3. PROTOCOL VERSION**

Version 1.0 21-11-2022 REF: 2021-05758-01

Version 1.1 22-06-2022 REF: 2022-02999-02

The study started following the amendments in version 1.1 and subsequent approval by the Swedish Ethical Review Authority.

### **4. FUNDING**

The project has received funding via Karolinska Institute from Hannover Re (100,000 SEK), Tornspiran Foundation (50,000 SEK), Lars Hierta Memorial Foundation (42,000 SEK), Magnus Bergvalls Foundation (100,000 SEK) and a grant from CIMED (region Stockholm) of 2,100,000 SEK.

## **6. INTRODUCTION**

### **6a. Background and rationale**

Although the clinical consequences of COVID-19 are still largely unknown, physicians are observing persistent symptoms such as muscle weakness, headache, fatigue, shortness of breath, palpitations, and tachycardia, as well as neurological and cognitive disturbances, in an increasing number of patients. While some reports suggest that 74-88% of hospitalized COVID-19 patients experience symptoms lasting longer than 50-80 days, including fatigue, shortness of breath, and limitations in physical functioning, other reports across all cases of COVID-19 suggest that at least 2.3% of infected individuals suffer from COVID-19 symptoms for longer than 12 weeks. This corresponds to tens of thousands of cases in Sweden alone.

In the past 18 months, we have conducted clinical physiology and neurophysiological examinations in patients with ongoing or previous COVID-19 disease. These examinations have included diagnostic methods including cardiac, pulmonary, and vascular function, but also neurophysiological examinations, including Postural-orthostatic tachycardia syndrome (POTS). The result of these examinations has not given a clear picture of the etiology of the symptoms, due to many reasons such as randomly selected patients, unclear basis for referral, and lack of reference values for this group of patients. Given the apparent variability of symptoms and signs of long COVID-19 that we experience in our clinical setting, there is value in comprehensively stratifying and characterizing patients based on their physiological function. This is important because of the clinical difficulties in distinguishing and recognizing the multifaceted symptoms and signs of long COVID-19, particularly in relation to muscle weakness and fatigue, but also to narrow the differential diagnosis. In addition, a better understanding of neuromuscular function in this patient group may lead to a more individualized rehabilitation program, considering neurophysiological limitations and disabilities.

Along with a better physiological understanding of this patient population, structured methods are needed to meet the demands of rehabilitation. In this context, a major challenge is that exercise intolerance is a common and significant problem for the majority of individuals in this patient group. Indeed, the recent World Physiotherapy briefing paper, stated that physical activity, including exercise, should be approached with caution and vigilance to ensure that rehabilitation programs are restorative and not worsening a person's symptoms both during and in the days following exertion. Inevitably, therefore, many primary care providers are reluctant to incorporate exercise into the rehabilitation program, which risks exacerbating physical deconditioning.

While the mechanisms of exercise intolerance in post-COVID-19 patients are largely unknown, plausible candidates include muscle deconditioning, orthostatic intolerance, dysautonomia, exercise hyperventilation, and exacerbated inflammation. A recent study reported that several patients had significant exertional dyspnea 3 months after the onset of COVID-19 symptoms, despite a relatively mild disease course. Exercise capacity was reduced in all patients, as most of them could not reach their predicted maximal workload and none of them reached their predicted  $\text{VO}_{2\text{max}}$ . An increased  $\text{VE}/\text{VCO}_2$  ratio was observed in

most patients, suggesting that hyperventilation-induced hypocapnia after infection and prolonged inactivity may be responsible for a variety of extremely disabling symptoms, POTS has also been mentioned as a possible physiological feature of long-COVID-19 patients. However, research in this area is conflicting, and the original clinical definition of the syndrome has since been diluted by the inclusion of other symptoms, risking some overlap with patients in other disease categories.

Another plausible mechanism relates to the immune system and cytokine profile. An adequate initial adaptive immune response to SARS-CoV2 is associated with asymptomatic or mild disease, whereas systemic inflammation is common in patients with severe disease. Persistent (up to 60 days) systemic inflammation is characterised by an IL-6 and TNF signature, accompanied by high numbers of effector CD4+ and CD8+ T-cells. Recently, it was observed that 60% of patients who reported post-exertional exacerbation of symptoms met the scoring thresholds used in people with myalgic encephalomyelitis/chronic fatigue syndrome (ME /CFS). It is therefore interesting to note that patients with ME /CFS have significant correlations between measures of T-cell metabolism and plasma cytokine abundance that differ from the correlations observed in healthy controls. These data suggest impaired systemic and T-cell metabolism, associated with persistent immune changes, which may be one of the underlying mechanisms behind the experience of fatigue and maladaptive to exercise response.

## **6b. Purpose and aims**

The post-COVID-19 syndrome poses an unprecedented challenge to modern society, affecting millions of people worldwide. Because persistent fatigue and exercise intolerance are among the most common complaints of these patients, the rehabilitation efforts required will likely be both complex and challenging. The overall goals of this project are to 1) assess whether post-COVID-19 patients experience symptom exacerbation and/or physical limitations following exercise 2) improve physiological understanding of symptom and mechanisms behind exercise intolerance in this patient population, and finally 3) provide knowledge that can be directly applied in the clinical setting to improve diagnosis, care, and individualized rehabilitation of patients with post-COVID-19 syndrome.

To explore these goals, following comprehensive physiological assessment, we will describe, in a randomized cross-over trial, the acute physiologic response to various exercise regimens and relate these to post-exertional symptoms in patients with long-COVID-19. The acute exercise response will be closely monitored after three different exercise modalities: continuous moderate aerobic exercise, high-intensity interval training, and strength training. The comprehensive set of physiological assessments at baseline, after acute exercise, and at the one-year follow-up, will include COVID-19-related symptoms, post-exertional symptoms, neurophysiological function, circulatory function, respiratory/ventilatory function, maximal oxygen uptake, strength, physical function, blood status, and cytokine profiling.

We believe that more detailed physiological characterization, along with a better understanding of the plausible mechanisms underlined exercise-induced symptom

exacerbation and/or exercise incapacity, are necessary to introduce viable rehabilitation programs in this patient population. This knowledge could also help in decision making on which tests should be performed in the clinical setting to improve care, rule out differential diagnoses, and drive the design of future targeted and individualized rehabilitation interventions for this vulnerable patient population.

## **7. OBJECTIVES**

### **7a. Primary objective and hypothesis**

Post-exertional malaise (PEM) symptoms of post-COVID-19 subjects and age/sex matched controls in response to three different exercise trials. The primary outcome is the comparison of the change in fatigue rating using the visual analog scale (VAS) 0-10 before and 48h after each training trial between the post-COVID-19 group and the control group. We hypothesize that the post-COVID-19 group will suffer from persistent fatigue at 48h after exercise compared to baseline, whereas control group will return to the baseline level at this time point.

### **7b. Secondary objectives and hypothesis**

Other PEM symptoms (muscle pain, joint pain, lymph nodes, concentration, memory, headache, fever, sore throat) will be assessed using VAS 0–10 before, after and 48h after 3 different types of exercise the post-COVID-19 patients and controls and compared between the groups. An additional 3 validated questionnaires are used: a) Multifunctional Fatigue Inventory (MFI), b) Profile of Mood States (POMS), and c) Somatic and Psychological Health REport (SPHERE) will be administered to participants before, immediate-, and 48h post-exercise to assess PEM. We hypothesize that the post-COVID-19 group will suffer from persistent fatigue at 48h after exercise compared to baseline, whereas control group will return to the baseline level at this time point.

Cardiopulmonary exercise testing (CPET) will be also performed in post-COVID-19 subjects and age/sex matched controls at 48 hours post different exercise trials to assess and compared the exercise (in)capacity. Peak volume of oxygen consumption ( $\text{VO}_{2\text{peak}}$ ), and other parameters, including ventilation and  $\text{VE}/\text{VCO}_2$  ratio,  $\text{O}_2$  saturation, heart rate, blood lactate, and rating of perceived exertion (RPE) using Borg scale will be also used to assess exercise capacity in all participants at 48 hours following each exercise trial. We hypothesize that post-COVID-19 group may have lower exercise capacity at 48h compared to controls.

Physiological (comprehensive) characterization post-COVID-19 subjects and comparison with age/sex matched controls will provide knowledge on the physiological phenotype of the post-COVID-19 group. Numerous clinical examinations will be used to assess the physiological function of post-COVID-19 patients and compared to age/sex matched controls. Specifically, echocardiography and arteriography will be used to assess cardiovascular function, spirometry to assess respiratory function, cardiopulmonary exercise testing and 6-min walk test to assess exercise capacity, handgrip and isokinetic dynamometer to assess the muscular strength of upper and lower body respectively, CO-rebreathing method to assess blood and plasma volume, and head up tilt-test to assess dysautonomia. In addition, neurophysiological assessment includes nerve conduction studies, sympathetic skin response, heart rate variability studies, and needle EMG. Questionnaires, blood samples and muscle biopsy will be also collected and compared between the groups.

Finally, physiological function at 1y follow-up in post-COVID-19 patients and age/sex matched controls will be assessed. Same clinical investigations as the

baseline assessment will be performed at 1y follow-up in post-COVID-19 patients and age/sex matched controls. Comparisons within and between groups from baseline and 1y follow-up will be performed.

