**Spirometry:** The procedure will be performed by a biomedical analyst using Jaeger MasterScreen PFT powered by SentrySuite, Hoechberg, Germany, according to hospital clinical guidelines following an established protocol. Participants will be seated comfortably, with a nose clip in place to ensure that breathing occurs exclusively through the mouth. The procedure will begin with a maximal inhalation, followed by a forceful and sustained exhalation into the spirometer. Participants will be encouraged to exhale with maximal effort until their lungs are completely emptied. Multiple trials may be conducted to ensure the accuracy and consistency of the results. The spirometry variables will be the forced vital capacity (FVC), forced expiratory volume in the first second (FEV1), FEV% (FEV1/ VC MAX), maximum vital capacity (VC MAX), total lung capacity (TLC), and diffusing capacity of the lungs for carbon monoxide single breath corrected for Hb (DLCOc SB).

**Cardiopulmonary exercise testing (CPET):** A CPET will be performed to assess cardiorespiratory fitness, monitoring with an ECG to rule out potential risks of the exercise sessions in the study and subsequent CPETs. The CPET will be conducted on an RE990 electronically braked cycle ergometer (Rodby Innovation AB, Hagby, Sweden) with an online gas collection system (Jaeger®, Vyntus CPX, CareFusion, Hoechberg, Germany) to analyze exhaled gases using the breath-by-breath technique, wearing a Hans Rudolph mask. The test will begin with a three-minute rest period during which heart rate (HR), blood saturation (SaO2), blood pressure (BP), and blood lactate accumulation (bLa) will be determined. After resting, participants will begin cycling for 3 minutes without resistance at a cadence of 60 revolutions per minute (rpm). After 3 minutes, resistance will be increased to 20 watts and then gradually increased by 10, 15, 20, or 25 watts per minute, with the goal of reaching maximal effort and VO2peak in 8–12 minutes after voluntary fatigue. Throughout the test, HR will be monitored by continuous 12-lead ECG recording, BP, and perceived exertion will be recorded every other minute of the test, and bLa concentration will be measured pre and 3 minutes after the test in a capillary sample from the earlobe using a Lactate Scout+ (SensLab GmbH, Leipzig,

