Germany). The test will be considered maximal ( $\text{VO}_{2\text{peak}}$ ) when two or more of the following criteria are reached: 90% of age-predicted HR ( $220 - \text{age}$ ), a respiratory exchange ratio (RER)  $\geq 1.1$ , a peak  $\text{bLa}$  of  $\geq 6 \text{ mmol}\cdot\text{l}^{-1}$ , or a perceived exertion  $\geq 18$ .  $\text{VO}_{2\text{peak}}$  will be determined as the highest 20-second average. Subjects will be verbally encouraged during the test to increase their motivation for maximal exertion.

**Arteriography:** Measurements of aortic pulse wave velocity ( $\text{PWV}_{\text{ao}}$ ) will be performed using non-invasive technique (Arteriograph, TensioMed Ltd., Budapest, Hungary). Participants will be rested in supine position for at least 10 minutes, and then a single upper arm cuff will be placed to measure  $\text{PWV}_{\text{ao}}$ . The device first measures the brachial blood pressure and then inflates the cuff to suprasystolic pressure to occlude the brachial artery. During this period, the cuff collects pure pressure signals and detects direct and reflected systolic wave peaks. The time difference between the early and late systolic peaks is equal to the time of the aortic pulse wave traveling down to the aortic bifurcation and back towards the heart. The aortic root-bifurcation transit time can be calculated, and by estimate the straight distance between the suprasternal notch and pubic bone (an acceptable estimate of the aortic length), the  $\text{PWV}_{\text{ao}}$  will be calculated by the software.

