## **20. STATISTICAL METHODS**

Analyses will be performed using IBM SPSS Statistics for Windows, version 29.0 (Armonk, NY: IBM Corp). To assess the primary outcome (post-exertional symptom exacerbation from baseline to 48h after each exercise), a mix-linear model was initially planned to analyse the differences in symptom changes following three exercise sessions (HIIT, MICT, ST), between the two groups (post-COVID-19 patients vs. control). Subject ID and the order of exercise sessions will be used as random effect in the mix-linear model. Pairwise comparisons will be performed when significant main or interaction effects are detected, using Bonferroni correction.

However, during data analysis, the aforementioned statistical plan was amended given the nature of the data (not normally distributed data). Particularly, a significant number of the control subjects responded “zero” change in the visual analog scale assessing the symptom exacerbation. As such, non-parametric tests (Mann-Whitney test, Kruskal-Wallis test) were used to compare differences in symptoms following exercise trials between the groups.

A mixed-linear model was used to analyze differences in continuous data (CPET variables, interleukin (IL)-6, Creatine Kinase) following three exercise sessions (HIIT, MICT, ST) between the two groups (post-COVID-19 patients vs. control). Subject ID and order of exercise sessions were used as random effect in the mix-linear model. Pairwise comparisons will be performed when significant main or interaction effects are detected, using Bonferroni correction.

For the physiological characterization assessments, two-tailed Chi-square test or Student t-test will be used to examine differences in categorical or continuous variables, respectively, between the post-COVID-19 patients and the control group.

Results will be presented as mean (SD), and significance will be set at  $P < 0.05$ .

Missing data will be treated as missing values in the statistical models, unless otherwise specified. In retrospect, there was no need for missing data imputation. Therefore, missing data were treated as missing values.

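### Section 7b reads heart rate, lactate and RPE at the 48-hour CPET as exercise capacity, the CPET procedure reads them as effort, and no workload or time point is set to separate the two

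*Combined protocol and SAP*

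**What the plan says.** Section 7b makes VO2peak and several other CPET variables the measures of exercise capacity 48 hours after each session. Among the latter, "heart rate, blood lactate, and rating of perceived exertion (RPE) using Borg scale will be also used to assess exercise capacity". The hypothesis they serve is: "We hypothesize that post-COVID-19 group may have lower exercise capacity at 48h compared to controls".

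The CPET procedure in Section 12 counts a test as maximal "when two or more of the following criteria are reached: 90% of age-predicted HR", an RER of at least 1.1, a peak lactate of at least 6 mmol/l, or perceived exertion of at least 18. The test ends at volitional fatigue. On sampling, the same section says that "HR will be monitored by continuous 12-lead ECG recording, BP, and perceived exertion will be recorded every other minute of the test". Gas exchange is breath by breath. Lactate is taken before the test and 3 minutes after it.

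Section 20 gives the analysis: "A mixed-linear model was used to analyze differences in continuous data (CPET variables, interleukin (IL)-6, Creatine Kinase) following three exercise sessions", by group, with subject and session order as random effects.

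The documents describe the 48-hour test in two ways. The exercise-trials text of Section 12 has it as a graded test to exhaustion, and Section 11a has it as a submaximal response.

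**The concern.** Three of the four signals that tell the investigators how hard a participant tried are also read as results about what the participant can do. In a test that the participant ends, heart rate, ventilation and lactate depend partly on the load at which it ended, and RPE at the end is expected to lie near the top of the scale. A lower end-test heart rate in patients therefore fits two accounts: reduced capacity, or stopping earlier with the same response at every load.

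The distinction matters in this trial. Patients are enrolled because exertion worsens their symptoms, which is a reason to stop early. The introduction also names exercise hyperventilation as a candidate mechanism. A stopping-time effect on heart rate or ventilation could be reported as physiology, and a real rise in effort at a given load could go unseen.

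**Working it through.** The plan gives no figure on this point to reproduce. The check has a textual part and an illustrative part.

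**1. Roles side by side.**

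| Variable | Capacity measure (7b) | Effort criterion (12) | Sampled below peak (12) |
|---|---|---|---|
| Heart rate | yes | yes | yes, continuous |
| Lactate | yes | yes | no |
| RPE | yes | yes | yes, every other minute |
| RER | not named | yes | yes, from gas exchange |
| Ventilation, VE/VCO2 | yes | no | yes |
| VO2peak | yes | no (the result being qualified) | not applicable |

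Neither Section 7b nor Section 20 says at what point in the test each variable is compared, which direction of heart rate, lactate or RPE means lower capacity, or how a test that misses the criteria is handled.

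**2. Could the analysis be restricted to maximal tests?** The ways to meet at least two of four criteria number C(4,2) + C(4,3) + C(4,4) = 6 + 4 + 1 = 11. RER alone is one criterion and cannot qualify a test, so all 11 include heart rate, lactate or RPE. Only 3 of the 11 (RER plus one other) rest on just one of those three. Restriction would select on variables that Section 7b treats as outcomes, while analysing every test without an effort term leaves effort and capacity mixed.

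**3. Illustration for heart rate.** The 30 per group comes from Section 9 (the synopsis says 40). The other inputs are assumptions that are not in the documents: one line of 0.5 bpm/W for everyone, peak load 200 W with SD 40, residual SD 10 bpm, one test per person, and patients stopping a fraction s earlier.

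- Mean difference in peak heart rate = 0.5 × 200 × s = 5, 10, 15, 20 bpm lower for s = 5, 10, 15, 20%.
- Control variance = (0.5 × 40)² + 10² = 500. Patient variance = (0.5 × 40 × (1 − s))² + 10².
- For s = 10%: patient variance = 18² + 100 = 424. SE = √((500 + 424)/30) = 5.55. Difference/SE = 10/5.55 = 1.80, against a critical t of about 2.00 on 58 df, which gives about 42%.

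The same steps for peak workload at s = 10%: difference 20 W, SDs 40 and 36, SE = √((1600 + 1296)/30) = 9.83, ratio 2.03, about 52%.

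| Patients stop earlier by | Peak heart rate difference | Significant, peak heart rate | Significant, peak workload |
|---|---|---|---|
| 5% | −5 bpm | 14% | 16% |
| 10% | −10 bpm | 42% | 52% |
| 15% | −15 bpm | 77% | 87% |
| 20% | −20 bpm | 96% | 99% |

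At a matched workload the true heart rate difference is zero by construction, so about 5% of trials are significant. With a slope of 0.3 bpm/W and the same SD in both groups, √((0.3 × 40)² + 10²) = 15.6, the heart rate figures are 11, 31, 59 and 83%.

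**4. Illustration for RPE.** Assume a true 2-point rise with SD 2 at a matched load. SE = 2 × √(2/30) = 0.516, ratio 3.87, power 97%. At exhaustion, assume an end RPE of 19 (SD 0.9) in both groups. The rejection rate is then 5%, because equality was assumed. This contrast shows what a ceiling would do. It is not evidence that one exists.

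**The case against.** The strongest reply is that the end-of-test reading is not in the plan. Section 7b names no time point, sub-peak heart rate and RPE are collected by design, and Section 11a calls the 48-hour CPET submaximal. This stands. A reader might infer that the plan has committed to comparing exhaustion values, or that RPE is unable to show a difference. The documents support neither. They support an unstated time point, with the exhaustion wording in Section 12 pointing one way and Section 11a the other.

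Second, read beside VO2peak, end-test heart rate, lactate, RPE and RER help to flag early stopping. That also stands. The fault lies in reading them as capacity without a rule, not in collecting them.

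Third, a reader might infer that VO2peak or peak workload escapes the problem. Neither does. In the illustration peak workload, which Section 7b does not list as an outcome, is more sensitive to early stopping than peak heart rate.

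Fourth, the illustration imposes one heart rate-workload line on everyone, although the CPET criteria scale maximal heart rate by age. It also uses one test per person, where the plan has three 48-hour tests in a mixed model. The percentages therefore show direction and rough size only, and no figure was produced for ventilation or VE/VCO2.

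**Conclusion.** The point holds in a conditional form. The same three variables are named as capacity outcomes and as effort criteria, and the stated model has nothing that ties them to a common load, to effort or to the baseline CPET. If end-of-test values are compared, they cannot by themselves distinguish lower capacity from earlier stopping. Under the stated assumptions, stopping 10% earlier alone would make peak heart rate differ significantly in about 42% of trials at 0.5 bpm/W, or 31% at 0.3 bpm/W. None of the slopes, SDs or stopping fractions comes from the documents.

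The matter is worth correcting because a better analysis is available from data already recorded. It concerns secondary outcomes only. The primary outcome, the change in VAS fatigue, is untouched.

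**What to change.** Amend Sections 7b and 20 as follows.

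1. Keep VO2peak as the main capacity outcome, with the participant's baseline CPET value as a covariate or as change from it. Add a sensitivity analysis that takes account of effort, for example through end-test RER. Do not exclude tests on the maximal-effort criteria, since those include the outcomes.
2. Analyse heart rate, ventilation, VE/VCO2 and RPE as change from the baseline test at a matched submaximal workload that all of the participant's tests reached and at which RPE was recorded. State that each participant's wattage increment is the same across tests, because the CPET procedure allows 10, 15, 20 or 25 W per minute and does not say this.
3. Report end-test heart rate, RER, lactate and RPE by group as effort descriptors. Lactate belongs only here, as it has no matched-load value.
4. Reconcile Section 11a with the exercise-trials text of Section 12 on whether the 48-hour test is submaximal or to exhaustion.

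The cost is revised wording and re-extraction from stored CPET files, with no new measurement. The common stage may be low in very limited participants. Some RPE values will be missing at the chosen stage, because load rises every minute and RPE is taken every other minute. Results from this change should be labelled as a revision, since Section 20 already reports analyses in the past tense.
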